**1.0. Introduction and Background**

The most common cancer in adolescents and young adults (YA, age 18-39) is lymphoma. Lymphoma is a cancer of the immune system treated with chemotherapy with or without radiation. While 60-80% of patients are cured, the treatment isn’t without toxicity. Throughout their therapy, patients can experience nausea, fatigue, insomnia and anxiety. Some may also have more serious side effects, such as infections or neuropathy. Once the cancer is in remission, the patient may still experience many symptoms that prevent them from returning to work or school, due to changes in weight, hair, deconditioning, fear of cancer recurrence and prolonged fatigue. Exercise has been shown to improve many symptoms in cancer patients. This has led to revised evidence-based fitness guidelines for cancer patients and survivors. Recommendations are to perform 30 minutes of moderate to vigorous physical activity (MVPA) three times per week (1). The most profound and significant benefit is in reducing fatigue, whereas the effect on other cancer symptoms is less clear. Furthermore, the role of exercise in reducing cancer related symptoms has been mainly studied in patients with breast and prostate cancer and not YA patients with lymphoma.

**2.0. Literature Review**

**2.1. Current Standard of Care:** Lymphoma is the 6th most common cancer in Canada and the most common cancer diagnosed in YA, with Hodgkin lymphoma (HL) and diffuse large B-cell lymphoma (DLBCL) being the main subtypes (2). Over 80% of patients are cured following the 4-6 months administration of multi-agent chemotherapy. More specifically, ABVD (doxorubicin, bleomycin, vinblastine and dacarbazine), is given once every 2-weeks to HL patients and RCHOP (rituximab, cyclophosphamide, doxorubicin, vincristine and prednisone) is given every 3-weeks to DLBCL patients. These drugs have considerable toxicities, which include cardiac and pulmonary toxicity, peripheral neuropathy and an increased risk of developing infections from immune suppression. Moreover, the administration of radiation therapy in combination with doxorubicin to early-stage HL and some DLBCL patients significantly increases the long-term risk of CVD. Patients who achieve a complete remission enter a “follow up” phase, where they are typically monitored with blood tests and physical exams every 3-months for 2 years, which is the period where the risk of relapse is highest. They are then seen every 6-months for 3 years and yearly thereafter.

**2.2. Patient Concerns and Relevance of Research Question:** While health care providers’ main concerns during the chemotherapy phase is toxicity (*e.g*., infections) that could delay treatment and compromise cure, the patients’ concerns are extreme fatigue, nausea, anxiety, insomnia, pain and poor **health related quality of life (hrQOL)** (3,4). Although these short-term complications are partially addressed with medications, including steroids, anti-emetics, anxiolytics, analgesics and sedatives, they too are not without their side-effects. In the follow-up phase, **fear of cancer recurrence** can be disabling, requiring referrals to psychologists in some patients (5).

**2.3. FITT Guidelines for Exercise in Cancer Survivors:** It is universally accepted that exercise reduces the risk of obesity, type II diabetes (DM2), osteoporosis and small vessel disease (SVD) in the general population. As such, the World Health Organization recommends that adults should engage in a minimum of 150 minutes of moderate to vigorous physical activity (MVPA) per week (6). While these guidelines were initially extended to cancer survivors, field experts have since reviewed the literature and recently published evidence-based guidelines for cancer survivors during and post-chemotherapy called the FITT guidelines (1). These guidelines recommend that cancer survivors perform exercise a minimum of 3-times per week (**F**requency), at moderate to vigorous physical activity (MVPA) (**I**ntensity), 30-min each session, for at least 8-12 weeks (**T**ime), with aerobic activity favored over resistance training (**T**ype). Compliance with these guidelines has demonstrated improvement in fatigue, anxiety, depressive symptoms, hrQOL and physical function in cancer survivors. Taken together, exercise may be a good intervention for lymphoma patients to minimize both short and long-term complications of therapy.

**2.4. Rationale and Knowledge Gaps:** Encouraging lymphoma patients to exercise during therapy is **not** routinely recommended by hematologists in Quebec. The primary focus during treatment is disease control while limiting toxicity (mainly infections), with the understanding that fatigue and anxiety will eventually subside with time. The international exercise guidelines are primarily based on studies performed in patients with breast and prostate cancer. These studies relied heavily on activity self-reporting, which have their limitations from relying on memory of activities done in the past or overinflated accounts from patients wanting to portray themselves in a socially acceptable manner (7) Thus, further studies using *methods that can accurately* determine if exercise is associated with improved bio-psycho-social health in lymphoma survivors are needed.

**3.0. Hypothesis and Objectives:**

The primary objective of this proof-of-concept study is to determine the feasibility of the Lymfit intervention for future application in a larger trial. The purpose is then to determine if a personalized fitness program, with the help of a fitness tracker (Fitbit), can improve their activity levels, quality life, and well-being. This proof-of-concept study also aims to examine any potential safely-issues related to the remotely delivered exercise program.

**4.0 Research Plan:**

**4.1. The Lymfit Intervention:** Both supervised training (*i.e.,* a coach) and activity trackers (*e.g.,* Fitbits) has great potentials improve adherence to exercise prescriptions (8,9). Each participant will be given a 12-week exercise program, which will be constructed based on the recommendations from the FITT guidelines for cancer survivors by a kinesiologist. The participants in the study will follow up with the kinesiologist every two weeks to discuss any necessary changes within the exercise prescription.

**4.2. Methodology:** This single arm proof-of-concept trial will be a phase one study of a larger randomized controlled trial (RCT). Ethics approval will be obtained from the Research Ethics Board (REB) at the Jewish General Hospital (JGH; Montreal, Quebec). Participants in the study will be prescribed a personalized exercise program for 12-weeks, and their physical activity will be monitored using a FitBit. We have recently developed “Lymfit”, a server that allows our team to retrieve and store data from Fitbit devices on a secure network at the JGH. Physical parameters including activity minutes, daily step counts, sleep time, sedentary minutes, will be collected from the participant’s Fitbit and are stored in the Lymfit server. To preserve patient confidentiality, we will de-identify patient data by assigning each patient’s Fitbit device with a name (*e.g.* Lymfit001) and an email (*e.g.* [contact]), such that Fitbit has no access to personal patient data other than the date of birth, height and weight. The participants will complete a set of study questionnaires at **baseline, and at 12-weeks** (post-intervention).

**4.3. Participants and Recruitment:**

***Inclusion criteria:*** 1) lymphoma patients who received initial diagnosis at the age of age 18-39, 2) approved by their hematologist as having no contra-indications to vigorous exercise, 3) receiving or has received chemotherapy with curative intent, 4) own a cellular phone that is able to download the Fitbit app and to complete the study questionnaires online, and 5) is comfortable with teleconferencing with at least one platform (Zoom or Teams).

***Exclusion criteria:*** 1) The patient has contra-indications to vigorous exercise, or 2) the patient doesn’t want to wear a fitness tracker due to various concerns as no Fitbit data would be collected.

***Number of subjects:*** This is a proof-of-concept study to determine if the implementation of the exercise program is feasible and acceptable in this patient population. A total of 20 participants will be recruited to participant in this study.

***Recruitment*:** They will be recruited by their hematologist at the JGH. The JGH treats 20-25 newly diagnosed HL and DLBCL/year, with both sexes represented ~equally.

**4.4. Procedures:**

After the hematologist briefly discusses the project with the patient, interested participants will be contacted by a research coordinator who will explain the study in detail and obtain informed consent. The research coordinator will register the participants on the Lymfit server and enter baseline demographics. Each participant will fill out the first set of questionnaires and be given an assigned Fitbit (e.g. Lymfit 001) and will be registered at the Fitbit server as [contact]. For this study, we will use the Fitbit Inspire tracker, which will be synced with the Fitbit App and downloaded to their phone. All Fitbits can retrieve the fitness data required for this study, the Inspire tracker was chosen because it was within the scope of this proposal’s budget. Data from the Fitbit needs to be synced to the Fitbit server at least twice weekly (the data stored on the device for 5 days). The data will be transferred to our secure server at the JGH every night. This server is protected by a firewall such that only the study investigators have access to the patient data.

We will ask patients to perform their baseline activity assessment during the first week with their Fitbit. After that first week, the kinesiologists will examine the baseline physical activity and sedentary behaviours of the patient and schedule an appointment with him/her using teleconferencing (e.g. zoom) due to the physical distancing measured imposed by the covid19 pandemic. The default intervention in the Fitbit tracker is to track and motivate participants to increase their activity each week until they reach the guidelines set for cancer patients (90 min/week). They will be given personalized instructions for exercise prescriptions based on their baseline fitness level and exercise history at baseline, and every two week-there-after (given by teleconferencing). For instance, for sedentary patients or symptomatic patients that lack any motivation to exercise, the initial goal would be to increase the step count and to decrease sitting time. The kinesiologist and patient can explore opportunities throughout the day to take a series of brief walks. As these small milestones are achieved, the goal would be to increase the duration of activity (more steps) and to increase the intensity of the activity (i.e. increase the heart rate to be considered “active” minutes by increasing the pace of walking or by walking up stairs). In more active patients, exercise will be tailored accordingly, and will not require that the patient engage in these activities at a gym, where exposure to potentially infectious contacts is increased. In motivated patients who have successfully achieved 90 min of MVPA/week, we will encourage them to gradually increase their activity to 50 min x 3 times/week to meet the Canadian general population guidelines (16). For the purpose of this study, Fitbit data will be collected from 0 to 12-weeks during the exercise intervention. Patients will be contacted by email if there is no activity detected from their Fitbit for over 12 hours and when the battery level is too low.

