**5.0. Data Analysis:**

Descriptive statistics will be used to provide a summary of the basic demographic and physical characteristics of study participants. For the feasibility outcomes, the retention rate will be calculated as a percentage of the total number of those who are initially enrolled, and any technical and safety issues will be documented by the study coordinator. Physiologic metrics will be reported using descriptive statistics (i.e., frequency, percentage, mean, standard deviation). For all metrics captured by the Fitbit (i.e., light activity, MVPA, sedentary time, total sleep time, and steps taken), the daily averages will be computed from week 0 to week 12.

Missing data: Any day with a daily step count less than the pre-determined cut-off of 1000 steps/day will be excluded from the daily average over a week. A day will be included in the seven-day average only if the participant had more than 1000 steps in the day. A cut-off point for four out of seven days will also be required for that week to be considered a valid daily average. If there are less than four valid days of data for that particular week, that week of data for that participant will be omitted in the analysis. If a non-compliant participant had more than four invalid weeks out of the 12 weeks, they will be considered a lost to follow-up.

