**8.0. Benefits:**

The patients will be able to access their own data in real time on their Fitbit device and phone, which will motivate them to become more active. Furthermore, they can consent to have their own results of this study as well as the final study results, an option that is available on the consent form. This research has the potential to directly and immediately benefit patients by improving hrQOL, cardiovascular fitness and if sustained, decrease long-term risk factors for cardiovascular disease, diabetes and osteoporosis. Given the benefits of exercise in the general population and other cancer survivors, we anticipate that the Fitbit intervention will increase physical activity and fitness in lymphoma survivors and that this will translate into an improved QOL and reduce the fear of cancer recurrence.

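### The Fitbit activity baseline is recorded with the motivating tracker already active, and week 0 is not tied to the start of the 12-week programme

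*Protocol*

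**What the plan says.** On the baseline, section 4.4 states: "We will ask patients to perform their baseline activity assessment during the first week with their Fitbit". The kinesiologist reviews that week once it is over and then arranges a teleconference to give the prescription. The interval to that appointment is not fixed. Of the device, the same section says: "The default intervention in the Fitbit tracker is to track and motivate participants to increase their activity each week". Section 8.0 (Benefits) says that patients can "access their own data in real time on their Fitbit device and phone, which will motivate them to become more active". Section 3.0 gives the purpose, after feasibility, as to "determine if a personalized fitness program, with the help of a fitness tracker (Fitbit), can improve their activity levels". The protocol describes no period with feedback off, no hidden display and no activity measure taken before the tracker is worn.

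On timing, section 4.1 states: "Each participant will be given a 12-week exercise program". Section 4.4 states: "Fitbit data will be collected from 0 to 12-weeks during the exercise intervention". Section 5.0 says that "the daily averages will be computed from week 0 to week 12", and it treats a non-compliant participant with more than four invalid weeks among 12 as lost to follow-up. A week is valid only if at least four of its seven days exceed 1000 steps; otherwise it is omitted. Week 0 is not defined anywhere.

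**The concern.** By the protocol's own account the tracker is meant to raise activity, and it is part of what is being evaluated. A first week of wear with feedback visible is then not a reference for programme plus tracker. It is a reference for what the kinesiologist adds once the tracker is already working. The protocol fixes this choice, and no later analysis plan can recover a baseline without the tracker.

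The week numbering raises a second, smaller problem. The prescription follows the first week, yet section 4.4 places all of weeks 0 to 12 within the exercise intervention, and section 5.0 uses both a 0-to-12 span and a count of 12. Which weeks count can decide who is classed as lost to follow-up. That may feed retention, the first feasibility measure in section 4.5.1. Finally, an invalid first week is dropped like any other, although it is the only activity baseline that the participant has.

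**Working it through.** The protocol states no effect size or power figure to reproduce. The check compares the passages and uses simple arithmetic. Every input marked as assumed is not in the protocol.

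**1. Effect of an active tracker on the baseline week.** Let B be activity without the tracker, D the true gain under programme plus tracker, and r the proportional lift from the tracker in the first week.

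Observed change = (B + D) − B(1 + r) = D − rB.

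With D = 5 min/day of MVPA (assumed):

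| B (assumed) | r = 0 | r = 10% | r = 20% | r = 30% |
|---|---|---|---|---|
| 10 min/day | 5 | 4 | 3 | 2 |
| 20 min/day | 5 | 3 | 1 | −1 |

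For any r above zero the observed change is too small. The direction follows from the protocol's own expectation that the tracker motivates; the amount cannot be obtained from it.

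**2. Counting the weeks.** Weeks 0 to 12 inclusive are 12 − 0 + 1 = 13 weekly averages if week 0 is a full week. The invalid-week rule counts 12. Two readings are possible:

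- Week 0 is the baseline and weeks 1–12 are the programme: 1 + 12 = 13 weeks of wear, 12 weeks of programme, rule applied to 12. This agrees with sections 4.1 and 5.0. Only section 4.4 is out of line, because week 0 then falls before the prescription.
- The 12 weeks run from issue of the Fitbit: 12 weeks of wear, of which at most 12 − 1 = 11 follow the first consultation.

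**3. What the count does to the lost-to-follow-up rule.** Let q be the probability that a week is invalid (assumed) and treat weeks as independent (assumed). With X ~ Binomial(n, q), P(classed as lost) = P(X ≥ 5):

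| q | n = 11 | n = 12 | n = 13 |
|---|---|---|---|
| 0.1 | 0.003 | 0.004 | 0.006 |
| 0.2 | 0.050 | 0.073 | 0.099 |
| 0.3 | 0.210 | 0.276 | 0.346 |

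Multiplying by the planned 20 participants: at q = 0.2, 20 × 0.050 = 1.0, 20 × 0.073 = 1.5 and 20 × 0.099 = 2.0 expected losses; at q = 0.3, 4.2, 5.5 and 6.9.

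**4. Invalid first week.** If week 0 carries the same q, the expected number of participants without an activity baseline is 20q: 2, 4 and 6 at q = 0.1, 0.2 and 0.3.

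**The case against.** The case for leaving the plan as it is has real substance.

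- **The timeline.** A reader might infer that there is no clear 12-week exposure, or that the programme falls one week short. The documents do not support that. Section 4.1 states 12 weeks, and taking week 0 as baseline reconciles sections 4.1 and 5.0. The 11-week result needs the less natural reading. What remains is an undefined week 0 and one phrase in section 4.4 that does not fit.
- **Dilution.** A reader might infer that averaging weeks 0–12 as one block shrinks any change by 1/13. Section 5.0 describes seven-day averages with validity judged week by week, not one pooled mean, so this does not stand.
- **Scope.** A reader might infer that the study has no clean baseline at all. Section 4.4 lists the first questionnaires together with, and ahead of, issue of the Fitbit. The problem is confined to the Fitbit metrics.
- **The contrast is defensible.** Section 4.1 describes the intervention mainly as a kinesiologist-built programme, and a week before the prescription is a fair reference for that. This stands, but it answers a narrower question than the one in section 3.0.
- **Consequence.** The primary objective is feasibility, the analysis is descriptive in a single arm of 20, and no formal change-from-baseline test is specified. This stands and keeps the point moderate. Section 3.0 still asks whether activity improves, and the first week is the only reference available for that.
- **Invalid first week.** Section 5.0 omits the week from the analysis; it does not hide it from the kinesiologist, who also uses exercise history. Emails after 12 hours without activity should make such weeks less common. Both stand, but neither supplies an analysable baseline when the week fails.
- **Feasibility of hiding feedback.** Nothing in the documents shows that goals or the display can be switched off, so the remedy cannot depend on it.

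**Conclusion.** The point holds for the Fitbit activity metrics. Their baseline is taken while a component of the evaluated package is active, so change from the first week describes the kinesiologist-led programme added to the tracker. It probably understates programme plus tracker, provided the tracker motivates as sections 4.4 and 8.0 expect. The size is not in the protocol. The illustration ranges from no bias to the loss of the whole gain, depending on assumed values.

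The week count is an ambiguity to be reconciled, not a proven contradiction. It reaches the primary objective only through the lost-to-follow-up rule. Moving between 12 and 13 counted weeks changes the expected number lost by about 0.5 of 20 at an assumed 20% invalid-week rate, and by about 1.4 at 30%, with weeks taken as independent. The missing fallback for an invalid first week follows directly from section 5.0.

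**What to change.** Amend sections 4.4 and 5.0 as follows:

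- Define week 0 as the baseline week before the first kinesiologist call, and extend it until four valid days exist.
- Number programme weeks 1–12 from that call, and reconcile the section 4.4 sentence that places week 0 within the intervention.
- Apply the invalid-week rule to weeks 1–12 only, time the final questionnaire to the end of week 12, and report week 0 separately from the programme weeks.
- Turn off activity goals and reminders during week 0 if the app allows. If it does not, state that change from week 0 excludes the tracker's own effect, and limit the conclusion on activity to the programme added to the tracker.

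The cost is protocol wording, a few extra days of wear for some participants and, if feedback cannot be suppressed, a narrower conclusion. Suppressing goals and reminders would also briefly hold back part of the motivating function that the protocol counts on.

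### For participants still on chemotherapy, a one-week activity baseline without recorded cycle day or treatment status lets cycle position or the end of chemotherapy pass for a change in activity

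*Protocol*

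**What the plan says.** Section 4.3 of the protocol admits a patient who "receiving or has received chemotherapy with curative intent". It sets no entry rule relative to a cycle. According to section 2.1, ABVD "is given once every 2-weeks to HL patients" and RCHOP "is given every 3-weeks to DLBCL patients". The same section gives the length of treatment: "Over 80% of patients are cured following the 4-6 months administration of multi-agent chemotherapy".

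Section 4.4 defines the activity baseline: "We will ask patients to perform their baseline activity assessment during the first week with their Fitbit". It adds that "Fitbit data will be collected from 0 to 12-weeks during the exercise intervention". Section 5.0 then indexes the tracker results by study week: "the daily averages will be computed from week 0 to week 12". Sections 4.2 and 4.5 place the questionnaires at baseline and at 12 weeks, and section 4.2 labels the second one post-intervention.

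The study has a single arm of 20 participants. Feasibility is the primary objective. Section 3.0 adds the purpose of finding out whether the programme "can improve their activity levels, quality life, and well-being". No section ties the tracker start, a weekly average or a questionnaire to a cycle day, provides for recording infusion dates, or separates participants on treatment from those who have finished.

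**The concern.** Section 2.2 names extreme fatigue, nausea and insomnia among patients' concerns in the chemotherapy phase. If these symptoms rise and fall within a cycle, activity may do so too. A seven-day baseline then catches one part of the cycle, and a later week may catch another. With no control arm, nothing in the design removes such a difference.

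Treatment status can also change during the study. A participant whose chemotherapy ends within the 12 weeks may become more active for that reason alone. The weekly averages as described could not separate either effect from a response to the programme. That weakens what the study can say about activity and quality of life, which the later randomized trial would draw on.

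**Working it through.** The protocol gives no figure of its own on this point, so there is none to reproduce.

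**Inputs from the protocol:** baseline window of 7 days (4.4); cycles of 14 and 21 days, and a course of 4-6 months (2.1); tracker data over weeks 0 to 12 (4.4, 5.0).

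**Assumptions:** activity in the infusion week is a fraction d below the other weeks, with d from 0.20 to 0.40; the protocol gives no value. There is no true change in behaviour. Entry is uniform over the chemotherapy course.

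**1. Share of a cycle covered by the baseline.** 7/14 = 50%; 7/21 = 33%.

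**2. Phase shift between two assessments** (interval modulo cycle length):

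| Interval | 14-day cycle | 21-day cycle |
|---|---|---|
| 77 days (first to last of 12 weeks) | 7 days | 14 days |
| 84 days (week 0 to week 12) | 0 | 0 |
| 91 days (12 weeks counted from the end of a baseline week) | 7 days | 7 days |

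Since 84 = 6 × 14 = 4 × 21, week 0 and week 12 match in both regimens if no cycle slips and treatment continues.

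**3. Week 0 against the mean of weeks 1-12.** These weeks hold exactly six 2-week or four 3-week cycles. With non-infusion weeks set to 1, their mean is 1 − d/2 or 1 − d/3.

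- Baseline in the infusion week, 2-week cycle: (1 − d/2)/(1 − d) − 1. For d = 0.20, 0.90/0.80 − 1 = 12.5%. For d = 0.40, 0.80/0.60 − 1 = 33.3%.
- Baseline in the infusion week, 3-week cycle: (1 − d/3)/(1 − d) − 1. For d = 0.20 this is 16.7%; for d = 0.40, 44.4%.
- Baseline in another week: −d/2 (−10% to −20%) or −d/3 (−6.7% to −13.3%).

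**4. Week 0 in the infusion week against a single non-infusion week.** 1/(1 − d) − 1 gives 25% to 66.7%. This is the extreme pairing.

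**5. Random start positions.** The expected absolute artefact is zero: for the 2-week cycle, +d/2 and −d/2 are equally likely. What remains is spread. If 10 participants were on a 2-week cycle (assumed), the standard error that cycle position alone adds to the group mean in step 3 is (d/2)/√10, or 3% to 6% of non-infusion-week activity. For the out-of-phase single week in step 4 it is d/√10, or 6% to 13%.

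**6. Chemotherapy ending during follow-up.** The share is 12 weeks divided by the course length in weeks: 12/17.3 = 69% for 4 months and 12/26 = 46% for 6 months.

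**The case against.** The strongest reply is that the stated schedule already contains the matched comparison. Sections 4.4 and 5.0 run from week 0 to week 12, which is 84 days, and the questionnaires are nominally 12 weeks apart. A reader might infer that the planned follow-up is out of phase with treatment, for example because the first and last of 12 weeks are 77 days apart. The protocol plans no 77-day comparison, so that inference fails. What stands is narrower. No contrast is fixed, section 5.0 speaks both of weeks 0 to 12 and of 12 weeks, and nothing says whether the baseline week lies inside the programme.

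A reader might also infer a one-directional bias toward apparent gain. That would need trackers to be handed out at one cycle position. Sections 4.3 and 4.4 say that the hematologist introduces the study and a coordinator then contacts the patient; no link to an infusion is stated.

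The within-cycle dip is likewise an assumption: section 2.2 describes symptoms of the chemotherapy phase as a whole.

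Finally, the choice of weeks to compare may properly sit in a statistical analysis plan, which is not at hand. This is fair for the summaries. But no analysis plan can match cycle positions or classify treatment status unless the dates are collected.

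**Conclusion.** The point holds in a limited form. It concerns only participants on chemotherapy, whose share of the 20 is not stated. For them, comparing the baseline week with other weeks or with the 12-week mean can produce or hide a change. Under the assumed 20-40% dip, an infusion-week baseline against the 12-week mean shows a gain of 12.5-33% (2-week cycle) or 17-44% (3-week cycle). The larger 25-67% applies only to the extreme single-week pairing and should not be read as the expected error. With random start positions the effect is mainly added noise.

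The 84-day comparison is sound while treatment runs on schedule. It fails when a cycle is delayed or when chemotherapy ends, which under uniform entry would apply to about 46-69% of on-treatment entrants.

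It would be too strong to say that the questionnaires share the problem in general. They do so only if the 12 weeks are counted from a programme start after the baseline week (about 91 days), if a cycle slips, or if chemotherapy ends. Nor are the feasibility conclusions weakened: retention, technical issues and safety (section 4.5.1) do not depend on cycle position.

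**What to change.** - Record infusion dates and the chemotherapy end date from the hospital chart.
- State that week 0 is the baseline week, and that week 12 and the final questionnaire fall 84 days after their baseline counterparts. If a cycle is delayed, use the nearest assessment at the same cycle position.
- For on-treatment participants, summarize the weeks between as whole-cycle averages, in 2-week or 3-week blocks. Compare these blocks with one another and not with the single baseline week.
- Show separately those on treatment throughout, those who finish during the 12 weeks, and those off treatment at entry. Cycle matching cannot help the middle group, so their change should be read apart.

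The cost is protocol wording, one extra chart item and a little analysis work, with no added visit, device or participant. The subgroups will be small in a sample of 20, so the display is descriptive only. The final questionnaire may move by a few days, or by about a week (91 − 84 = 7 days) if its date is now counted from the end of the baseline week.
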